## Abstract

**Background:**

Chronic cough, defined it lasts more than 8 weeks. The symptom is common, but highly troublesome, and it reduces quality of life. Despite much effort to develop a protocol for diagnosis and treatment of chronic cough, it remains problematic to determine its cause. As a result, treatment is often unsuccessful. Thus, there is much interest regarding the use of symptomatic drugs to control chronic cough.

*Maekmoondong-tang* is widely used in East Asian countries to treat chronic dry cough. Several experimental studies have reported that the herbal medicine has immunomodulatory and antitussive effects. Clinical studies involving *Maekmoondong-tang* have also been carried out; however, these studies have involved treating various diseases as a whole rather than chronic cough itself. Thus, we aim to evaluate the efficacy and safety of *Maekmoondong-tang* in chronic dry cough patients with a randomized controlled trial.

**Methods/Design:**

This study is designed as an exploratory, single-center, placebo-controlled, double-blind, randomized, parallel group clinical trial. Patients with dry cough that has lasted more than 8 weeks will be recruited, after a 1-week run-in period, and randomly allocated to either the *Maekmoondong-tang* treatment group or the placebo group. The patients will receive *Maekmoondong-tang* or placebo granules 3 times daily for 4 weeks, with a 2-week follow-up. The primary outcome is a 10-point cough diary that will be recorded on a daily basis. The secondary outcomes comprise a cough visual analog scale, the Leicester Cough Questionnaire (Korean version), the Pattern Identification for Chronic Cough Questionnaire, biomarkers, safety testing, etc. Adverse events will also be reported.

**Discussion:**

This trial will assess the efficacy and safety of *Maekmoondong-tang* in chronic dry cough.

**Trial registration:**

Korean Clinical Trial Registry (http://cris.nih.go.kr; registration number: KCT0001646). Date of registration: October 5 2015

## Background

Chronic cough, defined as lasting more than 8 weeks, is a common respiratory symptom among outpatients [1–3]. It is associated with a substantial deterioration in quality of life, with various effects on all aspects of health, such as retching, vomiting, chest pain, rib fracture, incontinence, fainting, and depression [2, 4]. The management and treatment of chronic cough is often unsatisfactory, although a few clinical guidelines are available [5]. The most common conditions that lead to chronic cough are asthma, upper airway cough syndrome, and gastroesophageal reflux disease with a normal chest radiograph [3]. However, in up to 46 % of patients, no single cause is evident [6], and the treatment success rate has been reported to be as low as 58 % [7]. The number of patients with unexplained cough who do not improve after cause-specific treatment is increasing; therefore, clinicians and patients alike are concerned about cough treatment [5]. Despite this, studies into the efficacy of antitussive drugs to manage chronic cough have yielded inconsistent results. Moreover, the agents used showed adverse effects [8], and evidence for the efficacy of inhaled corticosteroids (ICS), which are recommended for chronic cough, is not strong [9]. Therefore, a limited range of drugs is available to care chronic cough.

*Maekmoondong-tang* (MMDT; *Mai-men-dong-tang* in Chinese; *Bakumondo-to* or TJ-29 in Japanese) was introduced in the Geumgweyoryak, a classical textbook of traditional Chinese medicine [10]. MMDT, which consists of six herbs, is widely used to treat cough caused by lung *yin* deficiency, which is a common pattern in chronic dry cough according to traditional Korean medicine (TKM) [11]. Here, “*yin*” refers in general to body fluids, and “lung *yin* deficiency” denotes a shortage of *yin* of the lung; that is, a dry lung. This lung *yin* deficiency is manifested by unproductive cough, afternoon fever, night sweating, flushed cheeks, dry throat, red and dry tongue, etc. [12]. According to the Donguibogam, which was published in 1613 by the royal physician Heo Jun and has been a popular piece of TKM literature, MMDT is also used for heat-induced asthma, which is caused by the lung or stomach *yin* deficiency [13]. The immunomodulatory [14] and anti-asthmatic [15, 16] effects of MMDT have been investigated in several studies. A peripheral antitussive effect of MMDT has also been reported [17, 18]; that is, the drug can be used to treat coughs that are not controlled by central cough suppressants like codeine. The results of case–control clinical studies have shown that MMDT reduces cough hypersensitivity [19, 20], which is another recently proposed cause of chronic cough [21, 22]. MMDT clinical trials have been carried out, but have focused only on specific diseases, such as asthma [23], chronic obstructive pulmonary disease (COPD) [24], and post-infectious cough [25, 26], not on the symptom itself. To our knowledge, no clinical trials have studied the efficacy of MMDT on chronic dry cough with normal chest X-ray.

Therefore, we aim to investigate the efficacy and safety of MMDT for chronic dry cough. We will evaluate cough symptoms in terms of their intensity and severity using a cough diary, cough visual analog scale (VAS), and cough-specific quality of life questionnaire.

## Methods/Design

### Objective

The objective of this trial is to assess the efficacy and safety of MMDT for the adult patients with chronic dry cough.

### Hypothesis

We primarily hypothesize that 4 weeks of MMDT intervention eases chronic dry cough in adults more efficaciously than a placebo control. We will evaluate this hypothesis using a 10-point cough diary.

### Design

This study is an exploratory, single-center, placebo-controlled, double-blind, randomized, parallel group clinical trial. Figure 1 shows a flow chart of the study. Eligibility for the study will be decided on the basis of a daily cough diary, which participants will keep during the 1-week run-in period. Those with a cough diary symptom score of more than 2, as well as more than 10 entries in the cough diary during the run-in period, will be enrolled pending the inclusion and exclusion criteria below.

**Fig. 1 Fig1:**
[figure not shown]
Study flow chart

### Participants

#### Inclusion, exclusion, and withdrawal criteria

The inclusion criteria are: (1) age between 19 and 75 years; (2) chronic cough that has lasted more than 8 weeks; (3) dry cough (sputum frequency of 5 or fewer times per day, and sputum volume less than 10 ml per day, on the basis of the Sputum Severity Evaluation Standard of the Korean Ministry of Food and Drug Safety); (4) provision of written informed consent.

The exclusion criteria are: (1) abnormal pulmonary function test (forced vital capacity, or forced expiratory volume in 1 s, < 80 % of predicted); (2) abnormal chest X-ray; (3) acute respiratory disease, including upper respiratory tract infection, during the previous 4 weeks; (4) chronic pulmonary diseases (COPD, idiopathic pulmonary fibrosis, bronchiectasis, etc.) during the previous 2 years; (5) diagnosis of malignant tumor during the previous 5 years; (6) history of smoking (≥20 packs [400 cigarettes] during the participants’ lifetime); (7) treatment taking an angiotensin-converting-enzyme inhibitor at present or during the previous 4 months; (8) current or the precious 2-week use of antitussive drugs, glucocorticoids, leukotriene receptor antagonists, anticholinergic drugs, long-acting β2 agonists or any herbal medication; (9) antihistamine treatment during the previous 3 days; (10) aspartate aminotransferase (AST) or alanine aminotransferase (ALT) levels at least twofold higher than the upper normal limit, or a serum creatinine levels at least 1.2-fold the upper normal limit; (11) a mean cough diary score of less than 2 during the 1-week run-in period; (12) fewer than 10 entries in the cough diary during the 1-week run-in period; (13) pregnancy or breastfeeding; (14) illiteracy or cognitive impairment; (15) unsuitability as judged by the investigators.

The rejection and withdrawal criteria are: (1) treatment that might influence the results of the trial without the agreement of an investigator; (2) use of forbidden drugs, such as antitussives, glucocorticoids, leukotriene receptor antagonists, anticholinergics, and long-acting β2 agonists; (3) participants not following the protocol, or taking < 80 % of the prescribed doses; (4) a serious adverse event (SAE) during the trial; (5) voluntary withdrawal from the trial; (6) unsuitability as judged by the investigators.

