### Concomitant and forbidden drugs

If participants experience unbearable cough at night, taking one capsule acetylcysteine is permitted; this antitussive will be delivered to the patients along with the MMDT or placebo granules. If this does not improve the cough, the participant will visit the K-CTC for examination and appropriate management. The participants will be asked to record whether they take the antitussive agent or not. Other drugs that alleviate cough—such as other antitussives, glucocorticoids, leukotriene receptor antagonists, anticholinergics, short-acting β2 agonists, long-acting β2 agonists, and antihistamines—are prohibited. Drugs which are not related to cough symptoms will be permitted. The name, duration, and dosage of any other drugs taken will be recorded in the case report forms.

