### Statistical analysis plan

Data entry and management will be completed by an independent data administrator to ensure data accuracy. We will analyze the efficacy and safety of MMDT using the “intent-to-treat” (ITT) principle. Subordinately, we will also present the results of the analysis based on the “per protocol” principle.

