##### Per-protocol population

The per-protocol population will include patients who take more than 80 % of the prescribed doses of the study drug, fill in the daily cough diary on 80 % of the study days, and return their diary to the researchers.

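### Withdrawal for non-adherence or forbidden treatment is not separated from the end of outcome collection, so carried-forward values replace obtainable week-4 scores in the intent-to-treat analysis

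*Protocol article*

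**What the plan says.** All references are to the protocol article.

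- **Inclusion, exclusion, and withdrawal criteria.** The rejection and withdrawal list has six items. Item (3) covers "participants not following the protocol, or taking" under 80 % of doses. Ahead of it, item (2) names "use of forbidden drugs, such as antitussives, glucocorticoids, leukotriene receptor antagonists, anticholinergics, and long-acting β2 agonists", while the item that opens the list, (1), is "treatment that might influence the results of the trial without the agreement of an investigator". Further down, item (5) is "voluntary withdrawal from the trial".
- **Statistical analysis plan.** "We will analyze the efficacy and safety of MMDT using the" ITT principle; a per-protocol analysis is subordinate.
- **Intent-to-treat population.** At least one dose and at least one day of returned diary. There is no condition on adherence or other medication.
- **Per-protocol population.** The definition opens "The per-protocol population will include patients who take more than", and the dose threshold it then sets is 80 %. It adds conditions on diary completion and return.
- **Primary outcomes** and **Statistical analysis.** The primary outcome is the cough diary score at week 4, compared between arms by a t-test or Mann–Whitney test, with LOCF for missing data.
- **Concomitant and forbidden drugs.** For unbearable night cough, "taking one capsule acetylcysteine is permitted". If that does not help, the participant attends the centre for examination and management. Other cough-relieving drugs are prohibited.

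**The concern.** An ITT analysis compares the randomised groups whatever happened after randomisation. Missed doses and extra cough medication are the kind of event it is meant to absorb, with the outcome still measured. Here the same events are reasons to leave the trial. Stopping the study product and leaving the trial are different things, and the criteria do not distinguish them.

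The events may well be related to outcome. A participant whose cough is uncontrolled is more likely to seek another cough drug, and one who sees no benefit, or has recovered, is more likely to stop taking pouches. If the arms differ in how often or why this happens, the week-4 comparison rests partly on scores taken before the event. The plan would then have created missing primary outcomes that it could have avoided, and filled them under the assumption that the score stayed where it was.

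**Working it through.** **1. The plan's own figure.** Inputs from Sample size calculation: effect size 0.85, two-sided alpha 0.05, power 0.80, 20 % dropout, 1:1 allocation. The smallest n per arm at which the two-sample t-test (noncentral t) reaches 80 % power is 23 (power 0.805). Then 23 / (1 − 0.20) = 28.75, rounded up to 29 per arm, 58 in total. The stated size is reproduced and is not in dispute. The dropout allowance is 0.20 × 29 = 5.8, about 6 per arm.

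**2. Do the withdrawal rule and the per-protocol rule use the same dose cut?** Three pouches a day for 28 days is 84, dispensed as 42 at visit 1 and 42 at visit 2. Then 0.80 × 84 = 67.2. In whole pouches, 67 or fewer (67/84 = 79.8 %) meets withdrawal criterion (3), and 68 or more (68/84 = 81.0 %) meets the per-protocol dose condition. Over the full course the two rules divide participants at the same point, so a per-protocol condition is also being applied to staying in the trial.

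**3. When would a withdrawal cost the week-4 score?** Table 1 checks compliance at visits 2 and 3.

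- *Visit 2 (week 2).* Against all 84 pouches, anyone who has taken 25 or fewer of the first 42 can no longer reach the cut (25 + 42 = 67 < 67.2). If the rule is instead applied to the first 42 alone, the cut is 0.80 × 42 = 33.6. The article does not say which base is meant. On either reading, withdrawal here comes two weeks before the primary outcome.
- *Forbidden or unagreed treatment.* This can occur at any time before week 4. If the management given for unrelieved night cough includes a prohibited drug, criterion (2) applies.
- *Visit 3 (week 4).* The diary up to week 4 has already been kept. Under-dosing found then need not cost the primary outcome, though the week-6 assessment could be lost.

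**4. What happens to those withdrawn before week 4?** They meet the ITT definition and remain in the set. If diaries stop at withdrawal, the week-4 value is missing and LOCF supplies the participant's own last score.

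**5. How far apart can the target quantities be?** This is an illustration resting on assumptions that are not in the document. Let a share w of each arm meet these criteria, let those participants keep a fraction f of the 0.85 effect, and let the others keep all of it. With everyone followed, the effect is 0.85 × [(1 − w) + w × f].

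| w | f | Effect, all 29 per arm followed | Power | Shortfall from 0.85 |
|---|---|---|---|---|
| 0.2 | 0 | 0.68 | 72 % | 0.17 |
| 0.2 | 0.5 | 0.765 | 82 % | 0.085 |
| 0.2 | 1 | 0.85 | 89 % | 0 |

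For w = 0.1 and w = 0.3 with f = 0, the shortfall is 0.085 and 0.255. Analysing only the 23 adherent participants per arm (w = 0.2) would target 0.85 with 80 % power. LOCF on all 29 estimates neither quantity, so the table shows how much the choice of target can matter. It does not give the bias of the planned analysis.

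**The case against.** The strongest reply is that the ITT set is defined correctly and LOCF keeps every withdrawn participant in it. The trial is exploratory, and a condensed article may leave follow-up after withdrawal to the full protocol. The first part stands, and it rules out several stronger readings.

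- **A reader might infer that the ITT analysis collapses into the per-protocol one.** It does not. Someone withdrawn at visit 2 for low dosing is in the ITT set and outside the per-protocol set. The defect lies in how the week-4 value is obtained, not in who is counted.
- **A reader might infer that recorded scores are discarded when a participant is rejected at visit 3.** Nothing says so. LOCF applies to missing data, and a recorded score is not missing.
- **A reader might infer that any cough-relieving treatment leads to removal.** The permitted acetylcysteine capsule is not a stated reason, and criterion (1) applies only without the investigator's agreement.
- **A reader might try to size the bias.** Suppose 4 placebo and 1 MMDT participants are withdrawn, each truly 1 SD worse than the rest of the arm, and their scores are replaced by arm-typical values: (4 − 1)/29 = 0.10 SD, or 12 % of 0.85. LOCF does not do that. It carries forward the participant's own score, which may already be poor, and the true score after an effective cough drug could be better than the carried one. The counts and the 1 SD are also invented.

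The appeal to a condensed article goes only part of the way. The withdrawal criteria are printed as rules, in one list with leaving the trial voluntarily, so following the text as written ends participation. The exploratory label lowers the stakes but does not make an avoidable missing primary outcome desirable.

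**Conclusion.** The point holds in this form: criteria (1) to (3) end trial participation for post-randomisation reasons that may be related to outcome, without separating this from the end of outcome collection. For anyone withdrawn before week 4 on these grounds, LOCF stands in for a score that could have been observed, which undercuts the ITT analysis the plan puts first.

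Two assumptions carry this. Withdrawal is taken to mean leaving the trial, as its place beside voluntary withdrawal suggests, and diaries are taken to stop at that point. If the full protocol continues diaries after withdrawal, the point reduces to a wording correction. The dropout allowance is about 6 per arm, but the document does not say how much of it these criteria would produce. Neither the size nor the direction of the bias can be computed from it. The sample size of 58 is unaffected.

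**What to change.** In Inclusion, exclusion, and withdrawal criteria, state that meeting criterion (1), (2) or (3) does not end outcome collection. Diaries and the scheduled week-2, week-4 and week-6 assessments continue for every randomised participant who has not withdrawn consent, and all observed scores enter the ITT analysis. Let adherence and forbidden-drug use determine per-protocol membership only. LOCF would then be needed only where a score really could not be obtained.

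Whether the study product is stopped is a separate clinical decision that this change leaves alone. The withdrawal criteria and Concomitant and forbidden drugs must also be reconciled: the first lists antitussives as forbidden, while the second permits acetylcysteine and calls it an antitussive.

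The cost is a short amendment, which can apply only from now on because recruitment has begun, and some follow-up effort within visits and diaries already scheduled. The ITT effect may come out somewhat smaller, because it will include observed outcomes under poor adherence or added treatment.

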### Recruitment

Through advertisements and referrals, a total of 58 patients with chronic dry cough will be recruited at the Korean Medicine Clinical Trial Center (K-CTC) of the Kyung Hee University Korean Medicine Hospital.

### Ethics

This trial has been authorized by the Institutional Review Board of the Kyung Hee University Korean Medicine Hospital (approval number: KOMCIRB-150213-HRBR-007). The protocol accords with both the Declaration of Helsinki and Good Clinical Practice (GCP) Guidelines. Signed informed consent forms will be obtained from all eligible participants before enrollment.

This trial is registered with the Korean Clinical Trial Registry (registration number: KCT0001646).

### Randomization and Concealment

An independent statistician who is unware of the design and purpose of the study will generate a randomization table using R software (version 3.2.0; The R Foundation for Statistical Computing); specifically, a block size of 4 will be used, and the 58 patients will be randomly allocated group in a 1:1 ratio either to the MMDT treatment group or to the placebo control. The statistician will keep the randomization lists and inform the researcher of the matching cord number either by text message or via mobile communication application.

### Blinding

Participants, investigators, and the clinical trial pharmacist will be blinded to the treatment allocation throughout the course of the study. The placebo granules will be similar to the MMDT granules in appearance, taste, and scent. The manufacturer will label the random and product codes on the packaging, and the code labeling will conform to the GCP guidelines. The clinical trial pharmacist at the K-CTC will provide the packaged drugs to the patients on the basis of the randomization number. The statistician will uncover the blinding when necessary, such as an SAE occurs. A blinding test will be conducted to evaluate the success of blinding after 4 weeks of intervention.

### Intervention

#### MMDT

The MMDT group will receive MMDT granules (3 g/pouch, 3 times per day—before each meal—for 4 weeks; dosage based on the requirements of the Korean Ministry of Food and Drug Safety). The MMDT granules are manufactured as “Maekgeuron Granules” by Hanpoong Pharm & Food Co. Ltd. (Jeonju, Republic of Korea), a company that has obtained Korea Good Manufacturing Practice authorization. Both the MMDT granules and their ingredients have been approved by the Korean Ministry of Food and Drug Safety. Three grams (dry weight) of granules (water-extracted MMDT combined with starch and lactose) contain six herbs: *Ophiopogonis* Tuber (*Liriope platyphylla* Wang et Tang, family Liliaceae; 3.33 g), *Pinelliae* Tuber (*Pinellia ternata* Breitenbach, family Araceae; 1.67 g), *Glycyrrhizae* Radix (*Glycyrrhiza uralensis* Fischer, family Leguminosae; 0.67 g), *Zizyphi* Fructus (*Zizyphus jujuba* Miller var. *inermis* Rehder, family Rhamnaceae; 1.00 g), *Ginseng* Radix (*Panax ginseng* C. A. Meyer, family Araliaceae; 0.67 g), and *Oryzae* Semen (*Oryza sativa* Linné, family Gramineae; 3.33 g). This 10 g mixture yields 2.07 g of soft extract after boiling in water. With starch and lactose added, the final MMDT of 3 g is obtained by drying under reduced pressure. Each 3 g dose of MMDT contains 3.1 mg of glycyrrhzin acid and 0.31 mg of gincenoside Rb1 (Rg1). Voucher specimens will be reserved at the research library of Hanpoong Pharm & Food Company.

#### Placebo

The control group will receive placebo granules (3 g/pouch, 3 times per day—before each meal—for 4 weeks). The placebo was manufactured by the Jeonnam Bioindustry Foundation Food Research Center (JBF), following the placebo guidelines of the Korean Ministry of Food and Drug Safety. The granules do not contain any active ingredients, but are similar in appearance, taste, and scent to the MMDT granules.

All products were packaged by JBF (Naju, Republic of Korea). Either Forty-two MMDT or placebo pouches will be provided to each randomized participant at visit 1 (week 0 ± 3 days) and visit 2 (week 2 ± 3 days). The products will be stored at the K-CTC clinical research pharmacy in Kyunghee University Korean Medicine Hospital, and an independent and trained pharmacist will manage all procedures associated with the drugs. The study process is outlined in Table 1.

**Table 1 Tab1:** Study process: treatment and outcome measurements

Activity	Screening	Visit 1	Visit 2	Visit 3	Follow up
Time schedule	-Week 1	Baseline	Week 2	Week 4	Week 6
Window visit		±3 days	±3 days	±3 days	±3 days
Informed consent	X				
Demographics	X				
Cough symptom check	X				
Medical history	X				
Smoking history	X				
Medication history	X				
Safety test	X	X		X	
Chest X-ray	X				
Pulmonary function test	X				
Safety test	X				
Methacholine bronchial challenge test^a^	X				
Nasal endoscopy^a^	X				
Distribute cough diary card	X	X	X	X	
Randomization		X			
Height/weight/body mass index		X			
Vital sign		X			
Cough diary score		X	X	X	X
Cough visual analogue score		X	X	X	X
Leicester cough ques-tionnaire Korean versi- on		X		X	X
Pattern identification for chronic cough question-naire		X		X	
Cold-Heat pattern questionnaire		X		X	
Yin deficiency scale		X		X	
Hematological biomarker		X		X	
Immunologic biomarkers		X		X	
Investigational Produce		X	X		
Compliance			X	X	
Adverse events investi-gation			X	X	
Concomitant therapy eva- luation	X	X	X	X	

^a^The test will be performed as needed, according to the judgment of the investigator

